## Abstract

**Background:**

In many parts of the world, school-age children have high dental treatment needs; however, there is often low, or no, dental care provision. Although Atraumatic Restorative Treatment (ART) was developed to address this, its survival rate in occluso-proximal lesions is low. An alternative, the Hall Technique (HT) has shown better relative outcomes for occluso-proximal lesions, but has not been directly compared to ART or tested in field settings. This trial will compare ART and the HT for the most clinically- and cost-effective strategy for managing occluso-proximal lesions in primary molars, in a school setting, using low-technology and child-friendly dental techniques.

**Methods/Design:**

This two-arm, parallel group, patient-randomized controlled, superiority trial will have treatment provided in schools. Schoolchildren (*n* = 124, age 6–8) with at least one occluso-proximal carious primary molar lesion will have random allocation to treatment with ART or HT. Baseline measures and outcome data will be assessed through participant report, clinical examination and parent report/questionnaires. The primary outcome is survival rate, a composite measure of absence of Minor Failures (a defect in the restoration/crown, but not interfering with tooth health) and Major Failures (signs or symptoms of irreversible pulp damage, such as dental fistula/abscess, tooth fracture or failures that cannot be repaired). Secondary outcomes are: (1) child-reported discomfort, (2) childrens’ and (3) parents’ concerns around dental appearance and (4) acceptability of treatments, (5) occlusal-vertical dimensions (OVD) changes, (6) plaque index, (7) gingival health, (8) decayed, missing, filled teeth in permanent teeth (DMFT)/decayed, missing, filled teeth in primary teeth (dmft), (9) oral health-related-quality of life, reported by children and parents/caregivers, (10) the incremental cost-effectiveness, and (11) operator effect. A trained and calibrated examiner will evaluate the treated teeth after 1 week, then 1, 6, 12, 24 and 36 months post treatment. Kaplan-Meier and Cox regression tests will be used to investigate the primary outcome. The Mann-Whitney or *t* test, Friedman test, paired *t* test or Wilcoxon test and Ordinal Logistic Regression Analysis will be used to analyze the secondary outcomes.

**Discussion:**

The results of this trial will support decision-making by clinicians and policy-makers for managing occluso-proximal lesions in settings with constrained resources and limited dental access.

**Trial registration:**

www.clinicaltrials.gov, NCT02569047, registered 5 October 2015.

**Electronic supplementary material:**

The online version of this article (doi:10.1186/s13063-016-1270-z) contains supplementary material, which is available to authorized users.

## Background

The occurrence of cavitated caries lesions is still a problem in developed and developing countries [1], with an increasing prevalence, particularly in developing communities, conflicting with a general descending trend in prevalence worldwide [2]. In this context, the Atraumatic Restorative Treatment (ART) was developed. ART is a two-part strategy for the management of caries: the restorative step, and the essential adjunctive educational-preventive strategies [3]. The performance of ART restorations for longevity has been evaluated through clinical trials with the results of numerous studies showing that ART performs well for occlusal cavities in primary and permanent teeth [4–6] but there appear to be much lower success rates for occluso-proximal ART restorations in permanent and primary teeth [3, 4, 7–9]. Thus, occluso-proximal cavitations are now the main focus for contemporary research [10]. For primary teeth, reported restoration success rates range from 50 to 75 % in the first 2 years [11-14] with reported survival rates after 3 years of evaluation even lower [9], dropping to only 20 % in some cases [15].

Recently, the paradigm around the ideal management of carious lesions has been changing. Conventional restorative approaches, with its emphasis on the complete removal of carious tooth tissue followed by placement of a restoration [16, 17] has been substituted by more biological and less invasive approaches, focusing on biofilm control and disruption of the cariogenic biofilm environment to arrest caries [18–20]. The Hall Technique (HT) fits this philosophy. A preformed metal crown (PMC) is cemented, using glass ionomer cement (GIC), over the carious tooth, without tooth preparation or caries removal. This seals the cariogenic biofilm under the crown [21]. Studies have reported high survival rates of HT, with results of 98 % success rate after 1 year of evaluation [22] and 95 % after 23 [21] and 48 months [23].

Although HT is recommended for the management of dental caries in primary molars involving two or more surfaces and evidence of its efficacy had been published [21–23], these have all been carried out in clinical dental settings and have not been compared to ART. There are no clinical trials of the HT in a field setting and no direct comparisons of the longevity of occluso-proximal ART restorations with HT.

Therefore, the aim of this study is to evaluate the survival rate of occluso-proximal ART restorations compared with the HT in primary molars. Furthermore, self-reported patient discomfort, perception and concerns related to dental appearance, acceptance in relation to treatments reported by children and their parents/caregivers, evaluation of occlusal-vertical dimension (OVD), evaluation of cost-effectiveness, the impact of the two techniques on the oral health-related quality of life (OHRQoL) and the influence of the operator experience on the survival rate of treatments will be investigated.

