### Operators

Operators will be two final-year undergraduate dental students and one specialist in pediatric dentistry with 3 years of experience treating children. They were trained in both treatments. Training comprised a lecture on ART and the HT by clinicians experienced in the treatments and experienced in clinical trials. Also, the undergraduate students participated in a hands-on laboratory-based workshop for the handling and application of the materials and practicing carrying out both ART and the HT by clinicians experienced in the treatments. All operators will also undergo 2 weeks of training with children, using the different techniques before starting the study. This phase will be carried out in the field setting with similar children to those participating in the study, under the direct supervision of clinicians experienced in ART and HT.

Each child will be allocated to be treated by one of the operators with the aid of the random allocation list. All treatments will be performed on the school premises, in field conditions without the use of dental chair or other facilities from a clinical environment.

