#### Primary outcome

To verify the survival rate of treatments, as well as to evaluate the survival rate of the teeth examined, we will use a Kaplan-Meier survival analysis and the log-rank test. To evaluate the association between the outcome and patient variables we will use Cox regression test. The significance level for all analyses will be *p* <0.05.

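### The secondary objective on operator experience cannot be answered with one specialist and two students; it should be restated as an exploratory comparison of these three operators

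*Protocol article*

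**What the plan says.** The last paragraph of the Background gives, among the further aims, that "the influence of the operator experience on the survival rate of treatments will be investigated". The Abstract lists the same item more loosely, at the end of the secondary outcomes: "10) the incremental cost-effectiveness, and (11) operator effect".

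The Operators section states who delivers treatment: "Operators will be two final-year undergraduate dental students and one specialist in pediatric dentistry with 3 years of experience treating children". It describes training in both techniques and a lecture for all three. It adds that "the undergraduate students participated in a hands-on laboratory-based workshop for the handling and application of the materials", and then, for everyone, "All operators will also undergo 2 weeks of training with children, using the different techniques before starting the study". On assignment it says: "Each child will be allocated to be treated by one of the operators with the aid of the random allocation list". It does not say whether the randomization to ART or HT was stratified or blocked by operator.

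Under Statistical analysis, Primary outcome, the article says of treatment and tooth survival that "we will use a Kaplan-Meier survival analysis and the log-rank test", and then: "To evaluate the association between the outcome and patient variables we will use Cox regression test". Operator is not named there or under Secondary outcomes. The sample size section sizes the trial for ART versus HT only.

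**The concern.** Experience is a property of a class of operators. To attribute a difference to it, a study needs several people at each level, so that the difference between levels can be judged against the differences between people within a level. Here the experienced level holds one person. Any difference seen is the difference between that specialist and two particular students. The student-only workshop is a second feature that travels with experience level.

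Readers would use the answer. The article says the results are meant to support clinicians and policy-makers where resources are constrained, and its Discussion describes both techniques as suited to inexperienced practitioners. A sentence in the results about experience would be read as evidence on who can deliver them.

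**Working it through.** **1. The plan's own figure.** Inputs from the sample size section: ART survival 0.62 at 2 years, absolute difference 0.25 (so HT 0.87), two-sided alpha 5%, power 80%. 1:1 allocation is assumed.

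- Hazard ratio = ln(0.87)/ln(0.62) = 0.291.
- Freedman events = (1.96 + 0.84)² × ((1 + 0.291)/(1 − 0.291))² = 7.85 × 3.32 = 26.06.
- Pooled failure = 1 − (0.62 + 0.87)/2 = 0.255. Children = 26.06/0.255 = 102.2, so 103.
- 103 × 1.2 = 123.6, so 124.

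The stated 103 and 124 reproduce, so the sample size is not in question here. It supplies the event rate for what follows.

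**2. What the design can identify.** Let s² be the variance between individual operators on the log-hazard scale. The specialist-minus-students contrast carries person-to-person variance s²(1 + 1/2) = 1.5s² on top of sampling error. That term does not shrink as children are added. Even with unlimited children and s known, the 95% interval for an effect of experience would extend by a factor of exp(1.96 × s × √1.5) either side of the estimate:

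| s (assumed) | factor on the hazard ratio |
|---|---|
| 0.2 | 1.62 |
| 0.3 | 2.05 |
| 0.5 | 3.32 |

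The trial cannot estimate s at the experienced level at all. From the students it has one degree of freedom.

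**3. What happens if this is ignored.** Trials were simulated with no effect of experience, children split equally over three operators, 2-year survival of 0.62 and 0.87 by arm, and person-to-person SD s. The specialist's failure proportion was compared with the students' by a two-sided 5% test that treats children as independent.

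| s (assumed) | rejections, 103 children | rejections, 124 children |
|---|---|---|
| 0 | 4% | 4% |
| 0.2 | 8% | 8% |
| 0.3 | 12% | 14% |
| 0.5 | 25% | 27% |

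**4. Precision of the contrast, setting point 2 aside.** With an equal split, one third of children are treated by the specialist and two thirds by the students: about 41 and 83 of 124. The detectable hazard ratio at 80% power is exp(2.80/√(d × 1/3 × 2/3)) = exp(2.80/√(2d/9)), with d the number of failures. Power at a given hazard ratio is Φ(|ln HR| × √(2d/9) − 1.96). For 36 months, constant hazards are assumed: 0.62^1.5 = 0.488 and 0.87^1.5 = 0.811, so pooled failure is 0.350.

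| Horizon | Children | Failures d | Detectable hazard ratio | Power at a twofold hazard |
|---|---|---|---|---|
| 2 years | 103 | 26.3 | 3.19 | 39% |
| 2 years | 124 | 31.6 | 2.88 | 45% |
| 36 months | 103 | 36.1 | 2.69 | 50% |
| 36 months | 124 | 43.4 | 2.46 | 58% |

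**5. Arm by operator.** With 124 children there are 124/6 = 20.7 per operator and arm. Expected HT failures per operator are 20.7 × 0.13 = 2.7 at 2 years and 20.7 × 0.189 = 3.9 at 36 months. An interaction can be described but hardly estimated.

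**The case against.** The strongest reply is that this is the last of eleven secondary outcomes. It is absent from the questions set out in the Discussion, and the trial was never sized for it. The text says only that the influence will be investigated, and the Abstract's term, operator effect, is already close to a supportable aim. Low power for such an outcome is ordinary. All of this stands and limits the weight of the point, but it does not remove it. The Background names experience as the thing to be learned about, and neither more children nor a later analysis plan can supply more experienced operators.

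On training, all three operators learned both techniques and all had the supervised weeks with children. Only the workshop differs, and extra preparation may be thought part of being a novice. The training difference is therefore a secondary remark.

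A reader might go further and infer that the primary analysis wrongly ignores operator. The documents do not support that. The article does not name operator in the log-rank or Cox analyses, but it does not exclude it either, and adjustment factors are commonly left to an analysis plan that is not shown here. Nor does the article say that randomization was stratified by operator, so no stratification factor is shown to have been dropped. All operators deliver both techniques and are assigned with the aid of the random list. If that assignment is random and independent of arm, leaving operator out does not bias ART versus HT. It costs some precision and some protection against chance imbalance.

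A reader might also take the low power as rebutting a claim that students and specialist perform equally well. The protocol makes no such claim.

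**Conclusion.** The objective, as worded in the Background, cannot be met by the operators described. That conclusion rests on the text alone: one person at the experienced level, and a workshop named for the students only. It needs no numerical assumption.

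The figures are illustrations. The detectable hazard ratios of about 2.9 to 3.2 (2-year events) and 2.5 to 2.7 (36 months) assume an equal split over operators, the planned survival rates and, for the later horizon, constant hazards. The false-positive rates of about 8% to 27% depend on the assumed spread between operators.

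The point concerns what may be concluded from one secondary outcome. The ART versus HT comparison and its sample size are not affected.

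**What to change.** Reword the aim in the Background so that it matches the Abstract, for example: *to describe, as an exploratory analysis, differences in treatment survival between the three operators*. For this, fit a Cox model with arm and operator (three levels) as covariates and report hazard ratios with 95% confidence intervals. Add an arm-by-operator interaction labelled exploratory, with the failure counts per operator and arm beside it. State that the comparison concerns these three people and that no inference about experience will be drawn.

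Optionally, add operator as a three-level stratum in the log-rank and Cox comparison of ART with HT, fixed before outcome data are examined. This is separate from the model above, because a stratum gives no hazard ratio for operator. It would guard against chance imbalance between operators. The effect on power should be small but was not calculated.

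The cost is a change of wording and a few lines of analysis. No further children, visits or measurements are needed, and the operator of each child must be known for the listed outcome in any case.

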## Methods

### Ethical considerations and registrations

This protocol has been approved by the Research Ethics Committee of Dental School, University of São Paulo (protocol 1.293.935). The study protocol has been registered on ClinicalTrials.gov (NCT02569047 – 5 October 2015) and written following Consolidated Standards of Reporting Trials (CONSORT) guidelines for randomized trials of non-pharmacologic treatment [24] and the Standard Protocol Items: Recommendations for Interventional Trials guidelines for clinical trial protocols (SPIRIT - http://www.spirit-statement.org/spirit-statement/).

The study will be conducted in Tietê, a city in the state of São Paulo, Brazil. Informed consent will be obtained from children’s parents or guardians before participation in the study. Each child must also assent to participate. Participants’ confidentiality will be ensured using identification code numbers and the information recorded will be available only to researchers.

### Study design

This is a two-arm, parallel group, patient-randomized controlled, superiority trial with treatment provided in a school setting. The participants will be allocated to one of the two arms in order to compare different options for arresting occluso-proximal caries lesions (Fig. 1).

**Fig. 1 Fig1:**
[figure not shown]
Consolidated Standards of Reporting Trials (CONSORT) flow diagram of patient randomization

### Sample size calculation

The sample size was calculated based on the primary outcome – treatment survival, using the log-rank test in survival analysis. This involved a two-tailed test based on survival rate reported for ART (62 %) [13] after 2 years of follow- up, using the absolute difference of 25 % between groups, *α* of 5 % and power (strength) of 80 %. This gave an estimate of 103 children (with one tooth each treated within the study) to be recruited. After increasing by 20 % to compensate for participant loss to follow-up, the final sample size was set at 124 children (and 124 teeth).

### Participant selection

Children (6–8 years old) will be screened at seven primary schools and 124 who meet the inclusion criteria will be selected. Only the children whose parents or legal guardians signed the informed consent form and who assent to be part of the study will be included in the research. Children will be evaluated at the school in empty classrooms, prepared for the oral-examination, and receive instructions on oral health, particularly in relation to oral hygiene/toothbrushing and sugar consumption.

All phases of this trial will be carried out in the school where the child studies. First, the operators will carry out an intra-oral examination using a dental mirror, cotton rolls and periodontal probe. All information will be recorded in individual forms (see Additional file 1). The biofilm will be removed using gauze. The criteria for caries presence will be those of the World Health Organization (WHO) [25] and the decayed, missing, filled teeth in permanent teeth (DMFT) and decayed, missing, filled teeth in primary teeth (dmft) will be recorded [26].

### Participant inclusion criteria

The inclusion criteria for participants are: children whose parents or legal guardians accept and sign the consent form; children who assent to participation; aged between 6 and 8 years; exhibiting generally cooperative behavior; with good general health conditions; presenting at least one occluso-proximal lesion in a primary molar.

### Tooth inclusion criteria

Radiographic diagnostic facilities are not available in this setting, so only clinical diagnosis will be used. Specifically, the caries lesions inclusion criteria are: caries limited to the occluso-proximal surfaces and extending to dentine, accessible to hand instruments used in ART, absence of pain, fistula or abscess near the selected tooth; absence of pulp exposure; absence of pathological mobility; and cavity size smaller than 2.0 mm mesio-distally and 2.5 in the occluso-cervical and bucco-lingual directions measured with a WHO-graded periodontal probe.

In cases where the child has more than one occluso-proximal cavity eligible for inclusion in the study, only one cavity will be selected. In those cases, the child will have all teeth that meet the inclusion criteria numbered. Those numbers will be written on pieces of paper, folded and placed in an opaque envelope. An independent dentist who is not involved in the research will be responsible for selecting one of the papers, containing the tooth number that will be included in the research. Dentists from the municipality where the trial will be carried out, the operators of this trial and new groups of final year undergraduate dental students will perform all other necessary treatments. If necessary, the participants will continue to receive dental treatments in the municipality where the investigation will be carried out after completing this trial.

### Random allocation

The selected children will be assigned, by random allocation, to have their tooth treated with ART (control group) or the HT (experimental group). The randomization sequence will be generated electronically (http://randomization.com/) and to ensure allocation concealment, the randomly generated sequence will be sealed in opaque envelopes. An independent dentist from the municipality where the trial will be carried out will designate the allocation of each child using the opaque envelopes. Therefore, the envelope will be opened during the treatment, but only after the child is ready to receive treatment.

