First visit: • Assess the tooth shape, contact points/areas and the occlusion. • Use orthodontic separators to create space for fitting a Hall crown, unless there are no contact points. In order to protect the airway, the child will be sat upright • Thread two lengths of dental floss through the separator. Stretch the separator and floss taught and floss through the contact point briskly and firmly until the leading edge only is felt “popping through” the contact point. Remove the floss and make a second appointment with the patient 3 to 5 days later. Second visit: • Remove the separator with an excavator. • Gently remove loose plaque and food debris only from the cavity. • Assess the occlusion: measure the patient’s occlusal-vertical dimensions (OVD) with a millimeter probe using the distance between the most coronal points of the primary canines in order to assess the degree of overbite after mounting of the crown. • Protect the airway by placing a gauze swab square between the tongue and the tooth to be crowned. • Select the correct crown size (Stainless Steel Crowns, 3 M™ ESPE™, St. Paul, MN, USA). The crown should covers all the cusps and approaches the contact points, with a slight feeling of “spring back.” You should aim to fit the smallest size of crown which will seat. • Keep the treatment area free from saliva by isolating the tooth with cotton wool rolls. • Dry the inside of the crown with dry cotton pellets. • Mix the encapsulated glass ionomer cement (GIC) (Fuji I, GC Europe, Leuven, Belgium) for 10 seconds, according to the manufacturer’s instructions. • Load the crown generously with GIC (at least two thirds full). Avoid air blows and voids. • Place the crown over the tooth and seat the crown into place by finger pressure or ask the child to bite it into place. • Check the crown position as soon the crown is fitted. • Wipe away the excess GIC with a cotton wool roll or the gauze swab used to protect the airway. • Place a cotton wool roll between the crown and the opposing tooth and ask the child to bite firmly on the crown for another 2–3 minutes. • Remove excess cement, flossing between the contacts. • Blanching usually disappears within minutes. The occlusal discrepancy should resolve in a few weeks. • Measure the degree of bite opening and record in the notes. If excessive, then consider removing the entire crown. • Check the buccal relationship of the crowned tooth with its opposing number. If there is a displacing contact, resulting in a cross bite, then manage as for excessive bite propping.	

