### Follow-up examinations

At baseline, the outcome, child discomfort associated with treatment will be recorded:ART group: before and immediately after treatmentHT group (on two occasions): 1 – before and immediately after the placement of a separator when it is used, and 2 – before and immediately after the placement of the PMC

Perceptions and concerns related to dental appearance will be measured before and after treatment – for children and parents.

Questionnaires assessing acceptance of treatment will be given after treatment – for children and parents.

OVD measurement will be carried out before and after treatment.

Plaque index, gingival health, DMFT/dmft scores (before treatment) and the OHRQoL questionnaires will be recorded before treatment – for children and the OHRQoL questionnaire will be given to parents before treatment. Children will be assessed after 1 week, and then after 1, 6, 12, 24 and 36 months. At 1-week follow-up, the outcomes related to treatment evaluation, OVD measurement, plaque index and gingival health will be re-evaluated. At 1 month follow-up, the outcomes related to treatment evaluation, OVD measurement, plaque index and gingival health, DMFT/dmft scores and the questionnaire OHRQoL, will be re-evaluated. At other follow-ups (6, 12, 24 and 36 months), the outcomes related to treatment evaluation, OVD measurement, plaque index and gingival health, DMFT/dmft scores will be re-assessed (Table 6).

**Table 6 Tab6:** Sequence of procedures performed for each recruited participants

		ART group								HT group							
		Baseline		Evaluation						Baseline		Evaluation					
Event	Completed by	Baseline examination appointment	Treatment appointment	1 week	1 month	6 months	12 months	24 months	36 months	Baseline examination appointment	Treatment appointment	1 week	1 month	6 months	12 months	24 months	36 months
Consent/Assent	Dentist/Dental student	X								X							
DMFT/dmft	Dentist/Dental student	X			X	X	X	X	X	X			X	X	X	X	X
Plaque index	Dentist/Dental student	X		X	X	X	X	X	X	X		X	X	X	X	X	X
Gingival health	Dentist/Dental student	X		X	X	X	X	X	X	X		X	X	X	X	X	X
Instructions of oral hygiene/diet	Dentist/Dental student	X								X							
Orthodontic separators	Dentist/Dental student									X							
Treatment	Dentist/Dental student		X								X						
Wong-Baker faces scale (pre/post treatment)	Child		X							X	X						
Questionnaire about teeth appearance (pre/post treatment)	Child/Parent		X			X					X			X			

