Questionnaire about acceptance in relation to treatment	Child/Parent		X								X						
Measurement of OVD	Dentist/Dental student		X*	X	X	X	X	X	X		X*	X	X	X	X	X	X
Perceptions regarding OHRQoL	Child/Parent		X		X						X		X				
Treatment evaluation	Dentist/Dental student			X	X	X	X	X	X				X	X	X	X	X

***OVD will be measured before and immediately after treatment during the treatment appointment in Atraumatic Restorative Treatment (ART) and Hall Technique (HT) groups

*DMFT/dmft* decayed, missing, filled teeth in permanent teeth/decayed, missing, filled teeth in primary teeth, *OHRQoL* oral health-related quality of life, *OVD* occlusal-vertical dimension

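### The separator schedule reveals allocation before the OHRQoL and appearance baselines are taken, and places those baselines after treatment has begun for Hall Technique children with separators

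*Protocol article*

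**What the plan says.** - **Opening of the envelope.** Random allocation: "the envelope will be opened during the treatment, but only after the child is ready to receive treatment".
- **HT visits.** Table 2 gives HT two visits. At the first: "Use orthodontic separators to create space for fitting a Hall crown, unless there are no contact points". That visit ends with: "Remove the floss and make a second appointment with the patient 3 to 5 days later". The crown is fitted at the second visit.
- **Schedule.** In Table 6 the row "Orthodontic separators" has one mark, in the HT column for the baseline examination appointment. The treatment row is marked at the separate treatment appointment in both arms.
- **First measurements.** The rows "Perceptions regarding OHRQoL" and "Questionnaire about teeth appearance (pre/post treatment)" have no mark at the baseline examination in either arm; their first mark is at the treatment appointment. The Table 6 footnote says "OVD will be measured before and immediately after treatment during the treatment appointment".
- **Prose on OHRQoL.** The Follow-up examinations text places OHRQoL before treatment, in the same sentence as the plaque, gingival and DMFT/dmft scores. Table 6 puts those three at the baseline examination.
- **Discomfort.** HT children are scored on two occasions, the first being "before and immediately after the placement of a separator when it is used". ART children are scored on one.
- **Analysis.** The Secondary outcomes part of Statistical analysis tests the difference in CPQ and P-CPQ between 1 month and baseline with a paired t test. It compares appearance concerns and OVD over time with the Friedman test.

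**The concern.** A baseline should be taken before anyone can know the arm and before either treatment has started. Here the two arms appear to have baselines of different kinds. An ART child answers the OHRQoL and appearance questionnaires with nothing yet done. An HT child with a separator answers them after some days of wearing it, knowing which treatment is coming. CPQ has a symptoms domain and is given as an interview, so both the separator and knowledge of the arm could influence the answers. If the HT baseline is worsened in this way, the later change in that arm looks more favourable than it is. No analysis can recover a baseline from before the separator if none was collected.

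**Working it through.** No figure in the protocol is at stake, so the check sets the passages side by side.

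**1. When the arm must be known.** Separators are used in HT only. Table 6 places them at the baseline examination, and Table 2 places the crown 3 to 5 days later. Nobody can place a separator without knowing the arm. For any tooth with contact points, the envelope must therefore be opened by the end of the baseline examination visit. This holds for future ART children too, because their arm is unknown until it is opened. Table 6 gives ART children no treatment at that visit.

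**2. Whether the separator mark could be a misplaced cell.** The Wong-Baker row has an additional HT mark at the baseline examination and none there for ART. That matches the separator discomfort score in the prose, and Table 2 separately describes two HT visits. Three places agree.

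**3. Order of events in Table 6.**

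| Row | ART, first mark | HT, first mark |
|---|---|---|
| Plaque, gingival health, DMFT/dmft | Baseline examination | Baseline examination |
| Separators | None | Baseline examination |
| Wong-Baker | Treatment appointment | Baseline examination, then treatment appointment |
| OHRQoL | Treatment appointment (next: 1 month) | Treatment appointment (next: 1 month) |
| Appearance | Treatment appointment (next: 6 months) | Treatment appointment (next: 6 months) |
| OVD | Treatment appointment | Treatment appointment |

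For HT children with separators, the first OHRQoL, appearance and OVD values thus fall 3 to 5 days after placement. Table 2 confirms this for OVD by listing it at the second visit, after the separator is removed.

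**4. Effect on a change score.** Let s be the share of HT children who receive separators, and d the mean shift in their baseline score caused by the separator. Higher CPQ scores mean worse quality of life.

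- Shift in the HT mean baseline = s × d.
- Shift in the HT change (1 month minus baseline) = −s × d. If d is positive, HT appears to improve by s × d more than it did.
- Corresponding shift in ART from separators = 0.

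The protocol gives neither s nor d. Purely for scale, assume d = 2 to 5 points on the 0 to 116 CPQ scale. The bias is then 0 at s = 0 and 2 to 5 points at s = 1. These are assumptions, not estimates. Knowledge of the arm could shift answers further in either arm, in a direction that the documents do not settle.

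**5. What is not touched.** A between-arm comparison of the 1-month scores alone does not use the baseline and does not carry this bias. Treatment survival and its log-rank test do not use these measures.

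**The case against.** **The wording on the envelope can be read broadly.** Table 2 calls the separator appointment the first visit of the HT procedure, so opening the envelope there could count as during treatment. This softens the conflict for HT children. It does not remove it for ART children, who receive no treatment at that visit, and the late baselines remain on either reading.

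**Table 6 is weak evidence for questionnaire timing.** The prose groups OHRQoL with measures taken at the baseline examination. Parents complete their forms at home, so a parent mark under the treatment appointment cannot be literal. The table as read here also lacks a 1-week HT mark for treatment evaluation that the prose requires. This stands in part: parent timing is not fixed, and the intended child timing may be earlier. The protocol then still disagrees with itself and needs correcting.

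**OVD and appearance have no clear mechanism.** The OVD question is whether occlusion re-establishes after crown cementation, so a reading just before the crown is a sensible reference. No reason is evident why a separator would change views on appearance. This stands: the effect on both is uncertain, and OHRQoL is where bias is most plausible.

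**Discomfort is fully captured.** This stands too. Scores are taken around both the separator and the crown, and the choice of the HT score to be tested can be left to an analysis plan.

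**Stronger readings that the documents do not support.** A reader might infer that concealment at enrolment is broken. The conflict concerns when the arm becomes known relative to the baseline measures, not whether it could be foreseen when a child is enrolled. A reader might also infer a demonstrated bias of several CPQ points in favour of HT; neither the shift nor the share with separators is given.

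**Conclusion.** The concern holds for secondary outcomes. The protocol contradicts itself on when allocation is revealed. As scheduled in Table 6, the OHRQoL, appearance and OVD baselines of HT children with separators follow both allocation and the start of the intervention, while ART children have had no treatment. The CPQ and P-CPQ change to 1 month can be biased. The direction is probably toward HT, provided that the separator worsens symptoms at the time of the baseline interview. The size is s × d with both terms unknown, so no figure can be given. The conclusion assumes that Table 6 is followed for the questionnaires and that at least some study teeth have contact points. The primary outcome and the sample size are unaffected.

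**What to change.** - **Reconcile** the Random allocation section, Table 2, the Follow-up examinations text and Table 6 on when the envelope is opened. The separator schedule need not change for this.
- **Move the baseline questionnaires.** Complete the baseline OHRQoL and appearance questionnaires, child and parent, in both arms at the existing baseline examination, before the envelope is opened. Correct Table 6 to match.
- **OVD.** A reading can be added at the baseline examination in both arms, keeping the reading before the crown as the reference for the crown's effect.
- **Discomfort.** Report the HT separator and crown scores separately, so that the separator component is not dropped.

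**Cost.** The change uses an existing visit and existing instruments. Parent forms filled in at home would have to be returned before allocation. The Trial status section says that recruitment is under way, so children already enrolled keep the old baseline timing. They should be flagged in the analysis, because the data would otherwise mix two definitions of baseline.
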